# Comparison of effectiveness between warm acupuncture with local-distal points combination and local distribution points combination in breast cancer-related lymphedema patients: a study protocol for a multicenter, randomized, controlled clinical trial

**DOI:** 10.1186/s13063-019-3491-4

**Published:** 2019-07-05

**Keywords:** Acupuncture, Lymphedema, Breast cancer

## Abstract

**Background:**

Lymphedema is the most common complication after breast cancer treatment, but management of lymphedema remains a clinical challenge. Several studies have reported the beneficial effect of acupuncture for treating breast cancer-related lymphedema (BCRL). Our objective is to verify the effectiveness of warm acupuncture on BCRL and compare the effectiveness of a local distribution acupoint combination with a local-distal acupoint combination for BCRL.

**Methods:**

This is a study protocol for a multicenter, three-arm parallel, assessor blinded, randomized controlled trial. A total of 108 participants diagnosed as BCRL will be randomly allocated in equal proportions to a local distribution acupoint (LA) group, a local-distal acupoint (LDA) group, or a waiting-list (WL) group. The LA and LDA groups will receive 20 acupuncture treatment over 8 weeks with local distribution acupoint combination and local-distal acupoint combination, respectively. The WL group will receive acupuncture treatment after the study is concluded. The primary outcome is the mean change in inter-limb circumference difference from baseline to week 8. The secondary outcomes include volume measurement, skin hardness, common terminology criteria for adverse events 4.03 (edema limbs criteria), stages of lymphedema from the International Society of Lymphology, Disabilities of the Arm, Shoulder and Hand questionnaire, and the Medical Outcome Study 36-item Short-form Health Survey.

**Discussion:**

This study aims to provide data on warm acupuncture as an effective treatment for BCRL and at the same time compare the effectiveness of different acupoint combinations.

**Trial registration:**

ClinicalTrials.gov: Identifier NCT03373474. Registered on 14th December 2017.

**Electronic supplementary material:**

The online version of this article (10.1186/s13063-019-3491-4) contains supplementary material, which is available to authorized users.

## Background

Lymphedema is the most common complication after breast cancer treatment, with an average incidence rate of 21% [1]. Some of the symptoms associated with breast cancer-related lymphedema (BCRL) are discomfort, pain, heaviness, tightness, stiffness, weakness, and a decreased range of motion in the affected arm, which can cause severe physical morbidity. The swollen appearance of the arm can also cause psychological distress, such as depression and anxiety, since it is a constant reminder of breast cancer [2].

Although several treatment options are available, including manual lymphatic drainage, compression bandaging, and complete decongestive therapy, a clinical guideline on the integrative therapies used after breast cancer treatment reported that there were no A-graded or B-graded therapies to report for lymphedema [3]. Therefore, the treatment of lymphedema is difficult and probably requires multi-disciplinary attention. In several National Comprehensive Cancer Network guidelines, acupuncture is recommended for the supportive care of cancer to reduce symptoms and side effects of conventional cancer care [4]. Recent studies have begun to investigate the therapeutic effect of acupuncture on BCRL and results showed the potential of acupuncture treatment for BCRL [5–10]. However, previous studies were mostly pilot and observational studies with small sample sizes and, thus, the effectiveness of acupuncture needs to be further confirmed with a larger trial. In addition, no consensus has been reached on the choice of acupoints to achieve optimal results. For example, Cassileth et al. [8] performed a whole-body treatment that included acupoints on the abdomen, legs, and affected and unaffected arms, while Yao et al. [5] performed acupuncture treatment on the affected arm only. Although both acupuncture prescriptions were able to reduce arm circumference, which of the two provides better results remains unclear. Therefore, we propose a multi-center, randomized controlled trial to determine the optimal acupoint combination for the treatment of BCRL.

In this study, we aim to determine the effectiveness of warm acupuncture in the treatment of BCRL with a rigorous, larger, multicenter, randomized controlled trial. In addition, we will compare the effectiveness between different acupoint combinations. Specifically, we aim to determine whether a local-distal acupoint combination or a local distribution acupoint combination is more effective in the treatment of BCRL.

## Methods

### Study design

This study is a multicenter, three-arm parallel, assessor blinded, randomized controlled trial conducted in China. A total of 108 patients will be randomly assigned to local acupoint (LA) group, a local-distal acupoint (LDA) group, or a waiting-list (WL) group in a 1:1:1 ratio. The schedule of enrolment, interventions, and assessments is summarized in Table 1, and the study flow chart is shown in Fig. 1. Standard Protocol Items: Recommendations for Interventional Trials (SPIRIT) 2013 Checklist is attached as Additional file 1.

**Table 1 Tab1:**
[figure not shown]
Schedule of enrolment, interventions and assessments

LA, local distribution acupoints combination group; LDA, local-distal acupoints combination group; WL, waiting-list group; CBC, complete blood count; ECG, electrocardiography; CTCAE, Common Terminology Criteria for Adverse Events; ISL, International Society of Lymphology; DASH, Disabilities of the arm, shoulder, and hand; SF-36, the Medical Outcome Study 36-item Short-Form Health Survey

**Fig. 1 Fig1:**
[figure not shown]
Study flow chart

### Recruitment

Participants will be recruited from the Tianjin Medical University Cancer Institute and Hospital, Baokang Hospital Affiliated to Tianjin University of Traditional Chinese Medicine, The Second Affiliated Hospital of Baotou Medical College, Henan Cancer Hospital, Gansu Provincial Cancer Hospital, and Sichuan Cancer Hospital by billboard advertisement and practitioner referrals.

### Inclusion criteria

At least 6 months after breast cancer surgery and with persistent breast cancer-related upper extremity lymphedema for at least 3 months. Upper extremity lymphedema is defined as more than 2 cm circumference difference or 5% volume difference between the affected and unaffected arms.Presence of stage II or III lymphedema according to the 2016 consensus by the International Society of Lymphology [11].A Karnofsky Performance Score ≥70Men or women aged 18–80 yearsOut-patientsEstimated life expectancy >6 months

### Exclusion criteria

Bilateral BCRLTaking diureticsHistory of primary lymphedemaA diagnosis of severe heart, liver, kidney, or hematologic diseaseEdema caused by upper extremity disability or other conditions such as heart failure, kidney disease or malnutritionEdema caused by recurrent or metastatic breast cancerHypoproteinemiaInflammation, scar, or trauma at the site of operation, or other active skin infectionsUnable to self-care, history of psychological disorders, or unable to communicateReceived lymphedema treatment within the past 1 monthPregnancy or breastfeedingThe presence of electronic medical device implantsDenial to sign the informed written consent or unwillingness to conform to randomizationParticipation in other clinical trials during the study period

### Randomization and allocation concealment

After signing the informed consent, eligible participants will be randomly assigned to one of the three groups by center randomization. The Clinical Evaluation Center at the China Academy of Chinese Medical Science in Beijing will be responsible for the generation of a random number and group assignment, which will be provided through the website at http://118.144.35.11/crivrs/index.htm. The practitioner who will perform the acupuncture treatment will then assign the participant to that intervention.

### Blinding

The assessor who will collect the data and the statistician who will perform the statistical analysis will be blinded to group assignment. Acupuncturist blinding cannot be achieved due to the nature of the intervention. Participant blinding is limited to the LA group and LDA group, since the WL group cannot help but notice their allocation.

### Interventions

The acupuncture groups (LA and LDA group) will receive acupuncture treatments three times per week for a total of 20 treatments. The treatments will be performed by practitioners who hold a Chinese medicine practitioner license from the Ministry of Health of the People’s Republic of China. Practitioners will be instructed to achieve de qi sensation and then the needles will be retained for 30 min. Disposable, sterilized stainless-steel acupuncture needles will be used in the acupuncture groups (Huatuo disposable acupuncture needle, Suzhou Medical Co., Jiangsu, China, 0.25 × 40 mm). During the needle retention period, moxa cones (Mac mini needle moxa, Tianjin HaingLimSouWon Medical Co., Ltd., Tianjin, China, 2 cm) will be placed on the handle of the needles at specific acupoints. A piece of hard paper will be placed on the acupoint to prevent burning of the participants from falling ashes. The moxa cones will then be burned to delivery warm acupuncture. Additional hard paper will be added if the patient feels uncomfortable with the increasing temperature. All treatment that may affect the result of the study will be restricted, including surgical interventions, acupuncture, blood-letting, diuretics, exercise, complete decongestive therapy, compression therapy, and manual lymphatic drainage. Treatments that the participants had been using prior to the trial may be allowed at the discretion of the investigator after evaluation of the patient’s condition.

### Acupoint prescription set

Local points set: Waiguan (TE5), Quchi (LI11), Sidu (TE9), Shaohai (HT3), Naohui (TE13), and Xiajiquan on the affected arm.

Additional local points set: Chize (LU5), Quze (PC3), Zhizheng (SI7), Yangchi (TE4), Zhongzhu (TE3), Qingling (HT2), Tianjing (TE10), Jianyu (LI15), and two other points according to symptoms on the affected arm.

Distal points set: Waiguan (TE5), Quchi (LI11), Shaohai (HT3), Xiajiquan on the unaffected arm; Guanyuan (CV4), Qihai (CV6), Shuifen (CV9), Zhongwan (CV12), bilateral Sanyinjiao (SP6), and Yinlingquan (SP9).

Detailed location of the acupoints are shown in Fig. 2.

**Fig. 2 Fig2:**
[figure not shown]
Acupuncture points used in the study

### LA group

Participants will receive acupuncture treatment using the local points set plus the additional local points set (local distribution points combination). Warm acupuncture will be applied at Naohui (TE13), Quchi (LI11), and Sidu (TE9) if permitted, and one other acupoint according to the symptom on the affected arm.

### LDA group

Participants will receive acupuncture treatment using the local points set plus the distal points set (local-distal combination). Warm acupuncture will be applied similarly to the LA group, with the addition of Qihai (CV6), Shuifen (CV9), bilateral Yinlingquan (SP9), and Quchi (LI11) on the unaffected arm.

### WL group

Patients in the WL group will not receive any acupuncture treatment during the study. However, for ethical consideration, 20 free acupuncture treatments will be offered after the study is completed.

### Outcomes

#### Primary outcome measures

Various assessment methods are available, but circumference measurement is simple, convenient, low cost, and reliable [12]. Therefore, the primary outcome measures will be the mean change in inter-limb circumference difference from baseline to the end of the 8-week intervention. The circumference will be measured using a measurement tape (Hoechstmass Balzer Gmbh, Sulzbach,Germany) at the wrist crease, 10 cm above the wrist crease, elbow crease, 10 cm above the elbow crease, where the lymphedema is most severe, and at its corresponding location on the unaffected limb. The circumference difference will be assessed at baseline and before intervention at weeks 1–8.

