### Sample size calculation

According to the results of our preliminary trial (9 participants in the LDA group, 7 participants in the LA group, and 10 participants in the WL group), the biggest circumference difference after 20 treatments was 2.34 ± 1.6 cm, 3.32 ± 1.53 cm, and 3.74 ± 1.1 cm in the LDA, LA, and WL groups, respectively. According to the formula:$$ \mathrm{n}={\Psi}^2\left(\sum \left({Si}^2\right)/K\right)/\left[\sum {\left(\overline{Xi}-\overline{X}\right)}^2/\left(\mathrm{K}-1\right)\right] $$α = 0.05β = 0.10K = 3Ψ: K = 3, degree of freedom V1 = K–1 = 2; degree of freedom V2 = N–1, N is unknown, assume N as ∞, according to the T distribution critical values table when α = 0.05 and β = 0.10: Ψ α, β, K–1, ∞ = 2.52$$ \overline{Xi} $$ and Si represent mean number (X1 = 2.34, X2 = 3.32, X3 = 3.74) and standard deviation (S1 = 1.6, S2 = 1.53, S3 = 1.1) of group i according to the preliminary trial.$$ \overline{\mathrm{X}} $$= (X1 + X2 + X3)/K = (2.34 + 3.32 + 3.74)/3 = 3.13

The result of calculation was 30 participants in each group. Assuming a 20% dropout rate, a total of 108 participants are required with 36 participants in each group.

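### The timing of the primary circumference reading relative to the last session is contradictory: the stated readings do not coincide with the end of treatment under either session schedule

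*Protocol article*

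**What the plan says.** All statements are in the protocol article.

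- **Endpoint (Primary outcome measures):** "mean change in inter-limb circumference difference from baseline to the end of the 8-week intervention". The Abstract words it slightly differently: "The primary outcome is the mean change in inter-limb circumference difference from baseline to week 8". The Statistical analysis section compares changes up to the end of treatment by ANCOVA.
- **Readings (Primary outcome measures):** "The circumference difference will be assessed at baseline and before intervention at weeks" 1 to 8. The visible outcome text names no reading after the last session.
- **Session schedule (Interventions):** the two acupuncture groups "will receive acupuncture treatments three times per week for a total of 20 treatments".
- **Session schedule (Abstract, Methods):** "The LA and LDA groups will receive 20 acupuncture treatment over 8 weeks".
- **Planning data (Sample size calculation):** the pilot values were taken once the full course was complete: "the biggest circumference difference after 20 treatments was" 2.34, 3.32 and 3.74 cm in the LDA, LA and WL groups.
- **Control arm (WL group):** "Patients in the WL group will not receive any acupuncture treatment during the study".

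**The concern.** The endpoint is named by three descriptions that should mark the same moment: the end of an 8-week intervention, week 8, and the end of treatment. They mark the same moment only if the last session falls at the end of week 8 and the reading follows it. The stated frequency puts the last session in week 7, and the stated reading rule puts the measurement before a session.

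Two things are at stake. First, the quantity analysed may not be the quantity named, nor the one used for planning, which was observed after all 20 sessions. Second, the waiting-list arm is the control for the question of whether warm acupuncture works at all. A rule tied to sessions leaves its measurement day within week 8 undefined, so nothing in the visible text ensures that all three arms are read at the same time from randomisation.

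The same pre-intervention wording governs limb volume, skin hardness, CTCAE grade, lymphedema stage and DASH (weeks 1 to 8) and SF-36 (weeks 4 and 8), so it affects the secondary outcomes too.

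**Working it through.** **Inputs.** 20 sessions in total and three a week (Interventions); 20 sessions over 8 weeks (Abstract); readings before intervention in weeks 1 to 8 (Primary outcome measures).

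**Does the stated 8 weeks follow from the stated frequency?** Duration = sessions / sessions per week.

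- 20 / 3 = 6.67 weeks, not 8.
- 20 sessions in 8 weeks need 20 / 8 = 2.5 a week.
- Three a week for 8 weeks would be 3 × 8 = 24 sessions.

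So the two schedule statements do not fit each other. Each is taken in turn below.

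**Reading A: three a week, taken literally.** Six full weeks hold 3 × 6 = 18 sessions, leaving 2 in week 7 and none in week 8. Assume sessions on days 1, 3 and 5 of each week (the documents give no days). Session 20 then falls on day 45. Week 8 runs from day 50 to day 56, so a week-8 reading comes 50 − 45 = 5 to 56 − 45 = 11 days after the last session. All 20 sessions have been given. The reading is late rather than early, and there is no week-8 session for it to precede.

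**Reading B: sessions continue into week 8.** With at most three sessions in any week and at least one in week 8, listing all patterns that total 20 leaves 1, 2 or 3 sessions for week 8. A reading before the first of these comes after 17 to 19 sessions. If every week has two or three sessions, 2 or 3 are outstanding. On an even spread, 2.5 × 7 = 17.5 sessions are done and 2.5 / 20 = 12.5% are outstanding.

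**Waiting list.** This arm has zero sessions under either reading. The week is defined, but the rule supplies no day within it.

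**Illustration of size, Reading B only.** The pilot LDA–LA difference is 3.32 − 2.34 = 0.98 cm, with SDs 1.6 and 1.53. Assume that the whole difference builds up linearly with sessions. At 17.5 sessions it is 0.98 × 0.875 = 0.86 cm. Unadjusted two-sided Welch power at 5%:

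| Per arm | 0.98 cm | 0.86 cm |
|---|---|---|
| 28.8 (36 less 20%) | 65% | 53% |
| 36 | 75% | 63% |

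Under Reading A no sessions are outstanding, and this calculation does not apply.

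**The case against.** The strongest reply is that the two grounds for concern exclude each other. If the course ends after 6.7 weeks, the week-8 reading follows all 20 sessions and no treatment is missed. If sessions run into week 8, the 6.7-week figure does not apply. A reader might infer that the endpoint certainly misses the end of treatment. The documents do not support that: they do not say which schedule holds, and under one of the two the reading is simply some days late. This part of the reply stands.

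Four further objections carry weight.

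- **Unseen schedule.** Table 1 and Fig. 1 are not shown and may fix the final visit and the waiting-list visits. The Discussion mentions a 1-month follow-up that the outcome text does not list, so the visible text is not the whole visit list. Even so, a table of visits cannot make three a week for 20 sessions equal 8 weeks, or turn a pre-session reading into one at the end of the intervention.
- **Waiting-list anchor.** The Abstract's baseline-to-week-8 definition covers all three arms, so this arm does have a week. Only the day within it is undefined.
- **A late reading may cost little.** The Discussion reports that the preliminary effect lasted up to 1 month, so a gap of 5 to 11 days may matter little on the authors' own account.
- **The power illustration is fragile.** A reader might take the fall from 65% to 53% as the loss. The pilot 0.98 cm is a difference in post-treatment values with no baselines given, so scaling it assumes that all of it arose during treatment, and linearly. It rests on 9 and 7 patients (Welch 95% interval −0.72 to 2.68 cm), and the 0.12 cm shift is far inside that uncertainty. A plateau in response would shrink the loss.

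Nor does any passage say that schedules differ between patients. Early readings in some and late ones in others is a possibility if centres resolve the conflict differently, not something the plan describes.

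**Conclusion.** The point holds as a contradiction in the timing of the primary assessment. The session frequency, the course length, the named endpoint and the reading rule cannot all be true together. Under neither reading does the stated rule deliver a measurement at the end of the intervention: it comes either before the last 1 to 3 of 20 sessions, or roughly 5 to 11 days after the last one. The first range assumes at most three sessions a week with some in week 8; the second assumes a day 1, 3 and 5 calendar.

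The effect is a modest shift in timing, and its direction is unknown until the schedule is settled. No power loss should be claimed, because the figures above illustrate one reading under an undocumented linear response. The point still merits correction because it concerns the primary endpoint, the planning values come from after the full course, and the repair is nearly free. This is not a detail left to an analysis plan: the protocol states the timing, and states it inconsistently.

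**What to change.** 1. Reconcile the Abstract, Interventions, Primary outcome measures, Sample size calculation and Statistical analysis sections on the course length, the session frequency and the endpoint time. Which session schedule applies is for the investigators to decide.
2. Set the primary reading at one calendar time counted from randomisation, identical in all three arms and after the last planned session. Let it replace the pre-session week-8 reading, and use the same description of it in the endpoint definition and the ANCOVA.
3. Keep the earlier weekly readings for the trajectory analyses, and tie the waiting-list visits to weeks since randomisation.
4. Apply the same final time point to the secondary outcomes that share the pre-intervention wording, and check that Table 1 agrees.

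The cost is wording and, at most, moving one existing assessment. No procedure is added, because the new final reading takes the place of one already planned.

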#### Secondary outcome measures

Volume measurement is also commonly used for the evaluation of lymphedema and the mean change in inter-limb volume difference from baseline to the end of the 8-week intervention will be included as the second primary outcome measure. The volume of the affected and unaffected limbs will be measured by the volumetric measuring device (Baseline, USA) using the water displacement method, which is considered as the most reliable method for volume measurements [13]. The volume difference will be assessed at baseline and before intervention at weeks 1–8.

Skin hardness will be measured at places where the skin feels most tense to the touch by the NSCING SHORE LX-A durometer (Nanjing SuCe Measuring Instrument Co., Ltd., Nanjing, China). Skin changes such as increased tissue resistance and skin elasticity are often found in lymphedematous skin [14]. Our preliminary study found that patients felt more comfortable and less tense in the affected limb after acupuncture treatments. Therefore, we will use the muscle hardness tester to evaluate the effect of acupuncture on soft tissue tension. The change in skin hardness will be assessed at baseline and before intervention at weeks 1–8.

The Common Terminology Criteria for Adverse Events (CTCAE 4.03) [15] will be used to grade the severity of swelling using the edema limbs criteria. A grading of mild, moderate or severe swelling will be assessed based on the inter-limb circumference or volume discrepancy, anatomic architecture, appearance, or activities of daily living. The CTCAE 4.03 will allow us to evaluate the clinical significance of circumference change. The CTCAE 4.03 edema limb grading will be assessed at baseline and before intervention at weeks 1–8.

Stages of lymphedema from the International Society of Lymphology will be used to grade the severity of lymphedema [11]. Staging of 0, I, II, or III will be assessed based on severity of swelling, ability to reduce swelling by elevation, and skin changes. Staging of lymphedema will be assessed at baseline and before intervention at weeks 1–8.

The Disabilities of the Arm, Shoulder and Hand (DASH) questionnaire is a scale that consists of two concepts – functional status (part A) and symptoms (part B). The functional status part is further divided into three dimensions, namely physical, social, and psychological. The total score of the DASH ranges from 0 to 100, with higher scores representing worse symptoms and function. The DASH has good validity and responsiveness and it is recommended to assess upper extremity function in breast cancer survivors [16]. The validated Chinese version of the DASH will be used in this study [17]. The DASH will be assessed at baseline and before intervention at weeks 1–8.

The Medical Outcome Study 36-item Short-Form Health Survey (SF-36) is a commonly used instrument to assess quality of life and has good validity [18]. The SF-36 includes the following eight concepts: physical functioning, role limitations due to physical problems, social functioning, bodily pain, general mental health, role limitations due to emotional problems, vitality, and general health perception [19]. The validated Chinese version of the SF-36 will be used in this study [20]. The SF-36 will be assessed at baseline and before intervention at weeks 4 and 8.

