### Statistical analysis

A full analysis set will include all randomized participants who received at least one treatment and one follow-up. The principle of the last observation carried forward will be used in the case of missing data. The number of end point evaluations in each group will be kept the same as the number of participants in each group at the beginning of the trial.

A per-protocol set will include the following: (1) participants who meet the criteria of the protocol, (2) participants with measurable primary outcomes, and (3) participants without major violation of the protocol.

The statistical analysis of the primary outcome will be analyzed with a full analysis set and per-protocol set separately. The safety set will include all randomized participants who received at least one treatment.

Data will be coded and entered into SPSS (v.22) for statistical analysis. The Cochran–Mantel–Haenszel test will be used for analysis of center effect. Descriptive statistics of all sociodemographic and clinical data will be included. Continuous variables will be reported using mean and SD for normally distributed data or median and range for skewed data. Categorical variables will be expressed as number and percentage. For outcome measures, the mean differences from baseline values to the end of treatment will be compared using ANCOVA. Repeated measures analysis of variance (R-ANOVA) will be used to assess the inter-limb circumference difference, inter-limb volume difference and skin hardness between the three study groups. Inter-group differences in categorical data (CTCAE 4.03, stages of lymphedema) will be assessed using the χ^2^ test or Fisher’s exact tests (two-tailed), as appropriate. Linear mixed models (for continuous outcome variables) and generalized estimating equations (for categorical outcome variables) will be used to examine the change of intensity in inter-limb circumference difference and SF-36. *P* values of <0.05 will be considered statistically significant.

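### Volume is labelled both a secondary and a second primary outcome, and the article does not say which circumference site or summary is the primary variable

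*Protocol article*

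**What the plan says.** **Status of volume.** The Methods paragraph of the abstract gives one primary outcome, in the singular: "The primary outcome is the mean change in inter-limb circumference difference from baseline to week 8". It then states: "The secondary outcomes include volume measurement, skin hardness". In the body, volume appears under the heading for secondary outcome measures, yet the text there says that its change over the 8 weeks "will be included as the second primary outcome measure".

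**The circumference variable.** The Primary outcome measures section says "the primary outcome measures will be the mean change in inter-limb circumference difference from baseline to the end of the 8-week intervention". The tape is applied "at the wrist crease, 10 cm above the wrist crease, elbow crease, 10 cm above the elbow crease, where the lymphedema is most severe", with the matching place on the other arm. Read as a list, that is four landmarks and one most-severe site. Nothing says which of them, or what summary over them, is the variable to be analysed.

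**Planning quantity.** The Sample size calculation section uses "the biggest circumference difference after 20 treatments", with pilot values of 2.34 ± 1.6, 3.32 ± 1.53 and 3.74 ± 1.1 cm in the local-distal, local and waiting-list groups.

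**Testing rule.** The Statistical analysis section compares changes from baseline by ANCOVA and adds that P "values of <0.05 will be considered statistically significant". It gives no order of testing and no division of alpha.

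**The concern.** The two statements about volume cannot both stand. They matter most if circumference shows no difference and volume does. One reading of the article then calls the trial negative, and the other calls it positive on a primary outcome. If either outcome can carry the claim at 5%, the trial-level error rate exceeds 5%.

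The unnamed circumference variable leaves a similar choice open within the main outcome. A single landmark, the most-severe site, the largest difference, and a mean or sum over sites are different variables and could give different answers. The sample-size text points towards the largest difference, but the outcome section does not take that up. It is therefore also unclear whether the trial was sized for the variable it will analyse.

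**Working it through.** **1. The plan's own figure, to see which variable it uses.** The article's formula is n = Ψ² × (ΣSᵢ²/K) / [Σ(Xᵢ − X̄)²/(K − 1)].
- Mean variance: (1.6² + 1.53² + 1.1²)/3 = 6.1109/3 = 2.037.
- Between-group term: (0.6294 + 0.0348 + 0.3680)/2 = 0.5161.
- n = 2.52² × 2.037/0.5161 = 25.06, so 26 per group; the article states 30.

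That mismatch is a separate matter. What counts here is that every input is the biggest circumference difference after treatment. No volume figure enters, and no figure for another circumference summary.

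**2. Two primaries at 5% each, independent.** 1 − (1 − 0.05)² = 1 − 0.9025 = 9.75%.

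**3. Two primaries at 5% each, correlated.** Circumference and volume on the same arm should be positively correlated. The article gives no correlation, so the values below are assumptions. The set-up was three arms of 30 with no true difference, two normal outcomes, and an omnibus F test of each at 5% (2 and 3 × 29 = 87 degrees of freedom). There were 40,000 replicates per setting, and the result is the chance that at least one test is significant.
- correlation 0: 9.8% (agrees with step 2)
- correlation 0.5: 9.3%
- correlation 0.7: 8.5%
- correlation 0.9: 7.1%

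With one primary variable, or at correlation 1, the rate is 5%.

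**4. Keeping volume as a primary with an equal alpha split.** With the pilot circumference figures and the noncentral F distribution, 90% power for circumference needs 26 evaluable per group at 5% and 31 at 2.5%. At 30 per group, power is 93.9% and 89.6% respectively. Power for volume cannot be computed, because the article gives no planning values for it.

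**5. The circumference definitions side by side.**
- Abstract: one change in inter-limb difference, no site named.
- Primary outcome section: the same quantity, then five measuring places, with no rule for choosing or combining them.
- Sample size section: the largest difference, measured after treatment and not as a change.
- Statistical analysis: change from baseline by ANCOVA, again with no site named.

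No section connects the five places to one analysed variable. If the ANCOVA adjusts for baseline, analysing the change or the final value gives the same arm contrasts. The gap that remains is therefore mainly about which site or summary is meant.

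**The case against.** **It may be a slip.** The abstract, the section heading, the stated reasons for choosing circumference and the circumference-only sample size all point to volume as secondary. One phrase points the other way. This stands as evidence of intent and decides the direction of the fix. It does not remove the contradiction: the phrase stands in the body text and gives volume the same form of definition as the primary outcome.

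**An unseen document may set the rule.** Only an article is at hand, and an alpha split or a method of combining sites may be in the full protocol or SAP. The missing multiplicity rule alone would therefore be no finding. But the article does state the status of volume, twice and differently, and any fuller document would have to depart from one of those statements.

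**Stronger readings that the article does not support.**
- A reader might infer that five sites plus volume make six tests, any one of which could claim success. The article nowhere says that sites are tested separately or that one success suffices, and it speaks of the primary outcome in the singular. A mean, sum or maximum would make circumference one variable.
- A reader might infer that the worst site is chosen afresh at each visit, so that change compares different places on the arm. The article says neither that the site is re-chosen nor that it is fixed.
- A reader might infer that a site fixed as worst at baseline is the sample-size quantity. That quantity is the biggest difference after 20 treatments, with no statement that its site was fixed beforehand.

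**Conclusion.** The concern holds in two parts. First, the article contradicts itself on whether volume is primary. Taken literally, with either outcome sufficient at 5%, the false-positive rate is 9.75% under independence and about 7% to 8.5% at assumed correlations of 0.9 to 0.7. That any-one-suffices rule is not stated; the text only fails to exclude it. The rates are therefore what the literal wording permits, and exclude any further pairwise comparisons of the three arms.

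Second, the primary circumference variable is not identified among five measuring places, and the sample-size quantity is not carried into its definition. No error rate is attached to this part, because the article does not describe separate tests by site. The consequence is that the main result depends on a choice not yet recorded in the article, and that the power of the eventual variable is unknown unless it is the one used for planning.

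**What to change.** **Volume.** Delete the second-primary wording and call volume secondary throughout, in line with the abstract, the heading and the sample size. The cost is one phrase, and volume loses any primary status. Keeping it as a primary with a stated alpha rule would also resolve the contradiction, but would need planning values that the article lacks.

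**Circumference.** Before unblinding, name one variable obtainable from the data already collected. It could be the mean or the sum of the inter-limb differences over the four fixed landmarks. It could be the most-severe site, but only if its location was fixed at baseline and recorded. Make the other sites secondary, and state how the chosen variable relates to the biggest post-treatment difference used for planning.

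**Timing.** Recruitment was due to end on 2019/5/1, so 8 weeks of treatment for the last participant would end about 26 June 2019, before publication on 2019-07-05. A new measuring procedure may thus be too late, which is why the choice should rest on existing data. The assessor and the statistician are planned to be blinded, so a dated record of the choice is still feasible. The cost is wording, plus a short note that power for the chosen variable may differ from the planned value.
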